#### Primary outcome

Outcome measures will be used to carry out objective 3. The Modified Overt Aggression Scale (MOAS) [19] measures both the frequency (< 10 or > 10 observations) in the previous 7 days and the severity of aggression. It measures four types of aggression: (a) verbal aggression, (b) physical aggression against objects, (c) physical aggression against self, and (d) physical aggression against other people. Agreement between raters for MOAS total scores is (intra-class correlation coefficient (ICC)) of 0.93, verbal aggression (ICC = 0.90), and physical aggression against others (ICC = 0.90) [24].

#### Secondary outcomes

A battery of validated psychological and quality of life measures will be administered at pre-therapy, post-therapy, and follow-up including the Brief Symptom Inventory (BSI) [25], Novaco Anger Scale (NAS) [26], ICEpop CAPability Quality of Life measure for Adults (ICECAP-A V2) [27], and Glasgow Anxiety Scale for people with Intellectual Disability (GAS-ID) [28].

Frequency of routine clinical risk incidents such as periods of seclusion, use of rapid tranquilising medication, and use of prevention and management of violence and aggression techniques will be logged.

A semi-structured client interview will be conducted with participants following the end of treatment. Questions are designed to elicit responses from the participant about helpful and unhelpful aspects of therapy and the suitability and acceptability of treatment with additional questions about participant’s experience of taking part in the study. Thematic analysis [29] will be carried out on all interview transcripts.

Participants included in the single-case design component of the study will complete an additional continuous measure in the form of a daily anger rating scale. This is a visual self-report ‘thermometer style’ anger scale which has been adapted and simplified as recommended by our PPI (Patient and Public Involvement).

#### Study settings

Participants will be recruited from four NHS secure hospital sites in England including three medium/low secure hospitals and one high secure hospital.

##### Inclusion criteria for patients

An inpatient in a NHS secure hospital having been assessed with IQ of between 55 and 79 (within a range including moderate/mild/borderline intellectual disability). Age 18 to 60 years (within the age range for patients treated in the service) and able to give informed consent. Having a historic and continuing presentation of emotional control difficulties and/or observed aggression or antagonistic behaviour that puts the individual at odds with other people (as identified by the clinical team).The patient’s involvement in the study is supported by their responsible clinician and/or multidisciplinary care team.

##### Patient exclusion criteria

Unable to give informed consent. Having no clinical indicators for psychotherapeutic treatment. Planned discharge from hospital within 12 months of the start of the study.Receiving active assessment or treatment, including medication dose titration, for acute psychotic symptoms.

### Randomisation and allocation

Blinding to treatment is not possible in this study. The random allocation sequence was generated using a computer-based statistical software package. During the study, the random allocation sequence will be held by a research assistant who is wholly independent from the recruitment process. Allocation concealment will be in place beyond the first assessment point following which local therapists can request the allocation via email contact with a research assistant on a participant by participant basis. Participants can then be informed if they have been assigned to either interpersonal art psychotherapy or to the waiting list and re-assessed at 4 months by a research assistant.

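### Nothing keeps the 4-month outcome assessor unaware of allocation, although the primary outcome (MOAS) is rater-based; the plan should mask the assessor where it can, or say why it cannot

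*Protocol article*

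**What the plan says.** All the statements on allocation stand in the protocol article under Randomisation and allocation.

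- On blinding: "Blinding to treatment is not possible in this study". No distinction is drawn between participants, therapists and outcome assessors.
- On the sequence: it is to be "held by a research assistant who is wholly independent from the recruitment process".
- On release: "local therapists can request the allocation via email contact with a research assistant on a participant by participant basis", after the first assessment.
- On the later assessment: participants are told their arm and then "re-assessed at 4 months by a research assistant".

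Under Primary outcome, the MOAS covers the frequency and severity of aggression over the preceding 7 days. The section reports "Agreement between raters for MOAS total scores" as an intra-class correlation of 0.93, with 0.90 for verbal aggression and for physical aggression against others. It does not say who rates the scale or who supplies the observations.

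Under Treatment fidelity and contamination, a random 25% of session recordings is to be rated blind by a researcher with no other part in the study.

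**The concern.** Participants and therapists in a psychotherapy trial with a waiting-list control cannot be blinded. It does not follow that the outcome assessor must know the arm, and the article gives no reason for including the assessor in the statement. The one safeguard it names, independence from recruitment, protects against selection at entry. It does nothing for a rating made after allocation has been released.

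A scale on which someone judges the frequency and severity of aggression can be scored differently by a person who expects therapy to help. Good agreement between raters is no defence, because raters who share the same knowledge can share the same bias.

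Two things are at stake. The by-group MOAS means, which Statistical methods says will be estimated and used to inform future design, could be biased. The study would also miss the chance to learn whether masked assessment can be maintained in secure hospitals, which a definitive trial would need to know.

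**Working it through.** No stated figure depends on this point, so there is none to reproduce. The check sets the relevant sections side by side and then asks which planned estimates could be affected.

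**Step 1: who may know the allocation.** Randomisation and allocation gives three tasks to a research assistant: holding the sequence, releasing it to therapists, and re-assessing at 4 months. The only separation stated is between holding the sequence and recruiting. No sentence separates holding or releasing from assessing, and none withholds the allocation from the assessor.

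**Step 2: whether concealment fills the gap.** The section says "Allocation concealment will be in place beyond the first assessment point". Therapists can then request the allocation and participants can be told it. Concealment therefore protects the first assessment and ends at release, before the 4-month rating.

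**Step 3: whether another section supplies masking.** The only blind rating found is that of the fidelity recordings. It does not cover the MOAS. It does show that independent blind rating was thought workable for one part of this study.

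**Step 4: whether staffing would allow it.** Feasibility outcomes refers to research assistants in the plural, reporting patient feedback at each data collection point. Dividing the tasks need not call for a new role.

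**Step 5: which estimates would be affected.** Statistical methods plans means and SDs for the whole sample and by group, at each time point separately, and no hypothesis test. The Discussion names the SD and the future sample size as the uses. Suppose knowledge of the arm shifts every score in one arm by a constant d, in units of the within-arm SD.

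- Mean of that arm: moves by d.
- Within-arm SD: unchanged, because adding a constant leaves the spread as it was.
- Whole-sample SD, with equal arms and no other difference between arm means: multiplied by sqrt(1 + d²/4), because each arm mean lies d/2 from the overall mean.

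The document gives no value for d, and none is estimated here. Purely to show how flat the formula is:

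- d = 0.2: sqrt(1 + 0.04/4) = sqrt(1.01) = 1.005.
- d = 0.4: sqrt(1 + 0.16/4) = sqrt(1.04) = 1.020.

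The SD used for planning is therefore hardly touched by a constant shift. The by-group means take all of it.

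**The case against.** The strongest reply has four parts.

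**A condensed article leaves task assignment to the full protocol.** This has force for the question of which assistant does what. It does not cover the blinding sentence, which is a positive, unqualified statement, or the independence requirement, which is stated and limited to recruitment. A full protocol that masked the assessor would have to qualify that sentence.

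**Masking may not be achievable.** A 7-day aggression score probably draws on ward records or staff, although the article does not say so. The care team supports participation, is informed about the treatment and is on hand around sessions, so it may well know who attends therapy. A post-therapy interview about what helped could unmask whoever conducts it. This stands: masking the assistant would reduce the bias and would not abolish it. It is a reason to name the informant and record unmasking, or else to state openly that masking cannot be done.

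**The study tests no efficacy hypothesis.** This also stands, and it limits the harm to what step 5 shows.

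**More could be read into the text than it says.** A reader might infer that blinding has been abandoned altogether, but the fidelity recordings are to be rated blind. A reader might infer that one assistant both holds the allocation and rates at 4 months, but the article only fails to separate the roles. A reader might infer that the same staff administer the other questionnaires, but Secondary outcomes does not say who does. None of these readings is relied on here.

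**Conclusion.** The point holds in a limited form. The article makes a blanket statement against blinding, restricts the allocation holder's independence to recruitment, and leaves the 4-month assessor free to know the arm, while the primary outcome depends on a rater.

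The size of any bias cannot be quantified: the document gives neither a bias nor a target effect to set it against. No efficacy conclusion is at risk. What is exposed is the by-group MOAS means and the information on whether masked assessment is workable, which falls naturally under objective 3 (suitability of outcome data collection procedures).

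The statement that the SD is little affected assumes a constant shift in one arm; for the whole-sample SD it also assumes equal arms and no other difference between arm means. The article gives only the total of 20 randomised, not the split. A bias that grew with the severity of the behaviour could alter the within-arm SD too, and the document offers no way to judge that.

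The change is worth making because it is cheap and bears on the study's purpose. The gap does not invalidate the design.

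**What to change.** Amend Randomisation and allocation as follows.

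1. Limit the blinding statement to participants and therapists.
2. State that the assistant who holds or releases allocations conducts no outcome assessments.
3. State that the 4-month and follow-up assessor, drawn from the existing research assistants, is not told the allocation.
4. Have the post-therapy interview done after the outcome ratings, or by someone else.
5. Under objective 3, report unmasking events and the assessor's guess of allocation.

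Under Primary outcome, name who supplies the MOAS observations and who scores them, so that a reader can judge how far masking reaches.

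The cost is a division of tasks among assistants already planned, some care over the order of interview and ratings, and a short addition to the assessment form. The downside is that masking will be partial wherever ward staff or patients reveal the arm; the unmasking record will show how often. If the investigators judge masking unworkable on these wards, the section should say why and state unmasked assessment as a limitation.

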### Ethics and consent

Independent ethical approval has been granted by a local research ethics committee and the NHS Health Research Authority. The patients taking part in this study will have learning disabilities and be receiving inpatient care. Capacity to consent will be checked in the following ways: the Mental Capacity Act of 2005 will be followed and the patient’s responsible clinician will be advised that capacity to consent to take part in research is in the study inclusion criteria. Should there be any concern raised by the patient, their responsible clinician/care team or a member of the research team regarding capacity to consent an ‘empirical assessment of capacity to consent’ [30] will be carried out by a member of the research team. No further action will be taken if the patient is assessed to lack capacity. Patients will be initially approached by their responsible clinician or a member of their immediate care team to inform them about the study. If the patient would like further information about taking part in the study, this will be provided in written form via the study information sheet. Should patients require this information to be read aloud to them, this will be carried out by care staff who work closely with them and know them well. Patients will be given a minimum of 2 days to decide if they would like to take part in the study after receiving the study information sheet allowing them time to consider the information. Within the study information and consent form, patients will be informed that they can withdraw from the study at any time if they change their mind about participation, without penalty. If patients withdraw during the study, they will be asked if the researchers can include data collected up to that point in the study. Should they wish to proceed, they will be invited to a one-to-one meeting with a member of staff or research assistant and the study information and consent sheet will be reviewed with them and read aloud should they require this. Patients will be invited to have a member of staff who knows them well present at this meeting should they so wish. The voluntary nature of their involvement in this study and being able to withdraw from the study at any point without prejudice to further treatment will be explicitly stated on the study consent form. Recruitment of patients involved in current research or having recently been involved in research is not an exclusion criteria for participation in this study. We will not be asking potential participants to declare if they have recently been involved in research during any stage of the study.

### Confidentiality

All members of the study team are NHS staff and/or contracted to follow NHS trust policies and procedures for confidentiality and information governance in line with good clinical practice. No identifiable information about participants will be used in any report or publication. All personal data from participants will be anonymised using a unique identifier code number.

### Sample size

Twenty patients will be randomly assigned across both treatment allocations. The sample size for this feasibility study is limited due to a number of factors including limitations of time and budget, the intensity of the intervention, and the nature of the settings that it is taking place in. Participants are being recruited from four NHS hospitals in England with low, medium, and high levels of security. Smaller numbers of participants in multiple sites maximises the potential to assess feasibility objectives across a range of complex secure healthcare settings. This multi-site study will assist in future trial planning and inform feasibility from multi-level perspectives regarding issues and occurrences that could inform procedures related to recruitment, treatment acceptability, therapist adherence, and institutional support.

### Single-case design

Four patients (non-randomised) will be recruited for a single-case design component of the study to assess the acceptability of an attentional condition.

### Data management

Data will be collected at each study site including demographic data and current treatment; outcome measures will be collected during baseline, pre-therapy, post-therapy, and at follow-up assessment. Data management procedures will comply with NHS policies on information governance and data protection. Data will be anonymised using a unique participant identifier code and entered onto a password-protected NHS computer. Digital audio data will be wiped from the recording device after being transferred to an NHS password-protected computer. Consent to use an audio digital recording of therapy sessions is included on the consent form. Hard copies of questionnaires and interview transcripts will be stored in a locked filing cabinet in secure offices.

### Statistical methods

Simple descriptive estimation of parameters, for example mean and standard deviation (SD), will be carried out for the outcome measures. Estimation will be carried out using the population as a whole and by group. The numeric measures will be summarised using mean, median, SD, and interquartile range while categorical data will be expressed in terms of the proportion (or percent) of participants within each category and available sample size for each measure will be quoted throughout. Estimates of mean and SD for the measures will be carried out considering each time point separately. Feasibility study objectives will be summarised in the manner of categorical data. Estimates will be used to inform future study design.

### Data monitoring and interim analyses

A data monitoring committee will not be in place. Negative reactions and experiences of participants in the study and/or adverse clinical concerns can be raised by the participant, their responsible clinicians, or members of their immediate care team. It is an inclusion requirement that the participant’s responsible clinician and/or multidisciplinary care team support their involvement in the study and are therefore informed about the nature of the treatment being carried out.

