For people with learning disabilities, art psychotherapy uses art media as its primary mode of communication and having artistic skill and experience in art is not a prerequisite. This can offer the opportunity for expression and communication in the context of a psychological therapy to people who find it hard to express their thoughts and feelings verbally [9]. Through focusing communication around visual material there is greater potential for people with a learning disability, limited English proficiency (LEP), and/or a mental health difficulties, to develop understanding about themselves/their health or behaviour/and what they can do to enhance their well-being [11].

In offender populations a meta-synthesis review of the role of art therapies in therapeutic goals identified associations with improvements in emotional literacy, quality of life, and lower levels of arousal linked with feelings of anger [12]. Examples of ‘proof of concept’ work in adult offenders with learning disabilities have indicated positive outcomes from art psychotherapy in single-case designs. Reported improvements included reduced levels of aggression after receiving up to twenty individual sessions of treatment [13–15]. This preliminary work has led to the development of a working manual for interpersonal art psychotherapy that is being considered in this study.

Development of health technology and therapeutic interventions that support a reduction in aggressive behaviour in adults with learning disabilities has potential for clinical benefits for patients in England. Data collected as part of a national learning disability census identified a population of 3230 adults with learning disabilities being treated in hospital with a total of 1780 patients (55%) having one or more recorded incident of self-harm, accidents, physical assault, restraint, or seclusion (either ‘present’ or ‘severe’ enough risk to require hospital treatment). Within this group of patients, 5460 separate types of risk were recorded for either violence, self-injury, or damage to property [16]. An international literature review of inpatient violence and aggression [17] reported that patients treated in forensic settings are likely to be more violent than those in other settings such as psychiatric units.

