## Methods/design

### Study aims and objectives

The aim of the study is to establish the feasibility of conducting a definitive RCT of interpersonal art psychotherapy, with a primary focus on implementation and acceptability. The feasibility study will be carried out in four NHS secure hospital sites in England with treatment being provided by trained art psychotherapists who are registered with the UK Health and Care Professions Council (HCPC).

The study objectives for the assessment of feasibility are:Recruitment and consent, such as patients willingness to be randomised and clinicians willingness to recruit their patients into the study.Identifying issues related to seeking informed consent and risks of coercion, including potential for patients to participate in the study believing it will positively or negatively influence their inpatient treatment or detention under the mental health act.Procedures and materials, including suitability of study information, suitability of outcome measures, appraising burden of outcome measures and validated tools and suitability of outcome data collection procedures for maintaining data integrity from multiple study sites.Describing routine care and treatment as usual, identifying characteristics of treatment as usual across multiple sites, levels of high and medium/low security, and individualised patient care pathways.Attrition and acceptability, including rates of attendance for treatment and the acceptability of a novel attentional condition, reasons for non-attendance and/or drop-out, and lack of retention for data collection at the follow-up points.Identifying risks of contamination, such as patients on the waiting list receiving active components of the treatment during routine care and/or in the attentional condition.Treatment fidelity, identifying therapist adherence with the required activity in the treatment manual and piloting treatment fidelity checklist and procedures.

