### Harm

Interpersonal art psychotherapy and mindful colouring-in are non-invasive and non-intrusive interventions; however, individual psychological therapies can raise issues of concern for some patients. The main focus of the treatment in this study is to support a reduction in patient’s harmful and anti-social behaviours. To reduce the potential for participants to experience increased levels of distress, both in and following therapy sessions, the treatment will be conducted by qualified art psychotherapists in private/confidential rooms in familiar surroundings with trained members of the patient immediate care team on hand to support them should this be required.

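### Negative reactions reach the study by a passive route, and nothing asks both arms on one schedule whether anything got worse, so therapy-related distress may be under-reported

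*Protocol article*

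**What the plan says.** All references are to the protocol article.

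- **Data monitoring and interim analyses.** "A data monitoring committee will not be in place". On how problems become known: "Negative reactions and experiences of participants in the study and/or adverse clinical concerns can be raised by the participant, their responsible clinicians" or the immediate care team. No timing, question or form is attached to this.
- **Post-trial care.** The study information tells participants that they may also take concerns to the research team or to PALS.
- **Harm.** The text accepts that "individual psychological therapies can raise issues of concern for some patients". It then lists safeguards, introduced by "To reduce the potential for participants to experience increased levels of distress, both in and following therapy sessions". These cover prevention and support, not recording.
- **Background.** Art psychotherapy is said to offer a means of communication to "people who find it hard to express their thoughts and feelings verbally".
- **Feasibility outcomes.** Each of the seven objectives is matched to a data source, and none of them is harms. Research assistants already pass on patients' feedback whenever data are collected, but on questionnaire burden.
- **Secondary outcomes.** "Frequency of routine clinical risk incidents such as periods of seclusion, use of rapid tranquilising medication" and violence-management techniques are logged. Symptom, anger, anxiety and quality-of-life scales are given before therapy, after therapy and at follow-up. A post-therapy interview asks what helped and what did not.

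**The concern.** The hazard the article names is distress during or after sessions. The route it states for learning of that hazard depends on someone choosing to speak. For the patient this means speaking up, in a group for whom the case for the therapy is partly that verbal expression can be hard. The therapist, who is present at every session, is not among the reporters named in the data monitoring section. The research assistant, who sees participants at assessments, can be approached but is not asked to enquire about harm.

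The Background reports a review that found the evidence on benefits and harms of art therapy inconclusive, and this study is meant to inform a definitive trial. If few negative reactions are raised, the reader cannot tell whether few occurred or few were reported. A comparison between arms would be uncertain for the same reason.

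**Working it through.** **No figure to reproduce.** The article gives no adverse event rate, reporting rate, alpha or power. Its analysis is descriptive, and the sample of 20 is set by practical limits. The check is therefore mainly a comparison of the stated data sources with the stated hazard.

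**What each source would catch**

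| Source (section) | Depends on volunteering? | Both arms, same times? | What it would miss |
|---|---|---|---|
| Raised concerns (Data monitoring; Post-trial care) | Yes | Open to both, unscheduled | Anything nobody raises |
| Incident log (Secondary outcomes) | No | Not restricted by arm | Distress that leads to no incident |
| MOAS (Abstract; Primary outcome) | No | Both arms | Distress that is not aggressive; it covers the previous 7 days |
| Symptom and anxiety scales (Secondary outcomes) | No | Scheduled around therapy | Distress that starts and settles between time points |
| Post-therapy interview (Client interviews; Secondary outcomes) | No | No: a participant still waiting has no therapy to discuss | Recall only, after treatment ends |
| Session audio (Treatment fidelity and contamination) | No | No: therapy sessions only | A 25% sample is rated, for fidelity |

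Two details matter:

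1. The MOAS includes physical aggression against self, so it would detect some serious harm. If it is given only at the assessment points (an assumption), its 7-day window covers about 7/120 = 6% of the 4 months to re-assessment.
2. Statistical methods plans summaries by group at each time point separately. A group mean can hide one patient's deterioration.

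**Illustration of under-reporting.** Assumptions: 10 per arm (the article gives 20 in total and no allocation ratio), true share *p* with therapy distress, share *s* of cases reported. Expected count = 10 × *p* × *s*. Chance of recording at least one = 1 − (1 − *p* × *s*)^10.

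| *p* | *s* = 1 | *s* = 0.5 | *s* = 0.25 |
|---|---|---|---|
| 10% | 1.0 expected; 0.65 | 0.5; 0.40 | 0.25; 0.22 |
| 20% | 2.0; 0.89 | 1.0; 0.65 | 0.5; 0.40 |
| 30% | 3.0; 0.97 | 1.5; 0.80 | 0.75; 0.54 |

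For example, *p* = 20% and *s* = 0.25 gives 1 − 0.95^10 = 0.40.

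**Illustration of unequal reporting.** Take a true rate of 20% in both arms, with 80% of cases reported in one and 40% in the other. The expected counts are 10 × 0.2 × 0.8 = 1.6 and 10 × 0.2 × 0.4 = 0.8, a two-fold difference produced by reporting alone. Swapping the reporting rates reverses it. Nothing in the article says which arm would report more.

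**The case against.** The strongest reply is that harms do not depend on volunteering alone. Incidents are logged, the MOAS goes to both arms, anxiety and symptom scales are scheduled, unhelpful experiences are asked about after therapy, and reasons for drop-out fall under objective 5. That is correct. A reader might infer that harms surface only if someone volunteers them; these sources show otherwise. What they lack is designation as harm data and a common question to both arms.

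Three further inferences also go too far:

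- **Fear of consequences.** Objective 2 mentions patients "believing it will positively or negatively influence their inpatient treatment or detention under the mental health act". This concerns beliefs that might lead someone to take part. Reading it as fear of reporting distress is an extension the article does not make.
- **Clinicians as gatekeepers, therapist alone.** The research team and PALS are stated alternatives, and the Harm section has care staff nearby during sessions.
- **Few concerns taken as acceptability.** Acceptability is judged on attendance, interview reports, retention, perceived appropriateness and willingness to adhere, not on a count of raised concerns.

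Finally, this is a condensed article, and the full protocol may hold an adverse event procedure. Absence of such detail is no error. The point rests instead on the mechanism the article does state, in two sections devoted to monitoring and harm. If the full protocol solicits harms actively in both arms, the point is met.

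**Conclusion.** The point holds in a limited form. The stated route for negative reactions is passive, and no source described asks both arms on the same schedule whether anything got worse. Therapy-related distress that is not aggressive, or that resolves between assessments, may be under-reported.

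Reporting may also differ by arm: allocation is unblinded, the therapy arm has 15 extra contacts, and the interview is tied to therapy. It would be tempting to say that harms will be under-counted and counted unequally. The documents do not support that certainty. The same reporters are named for both arms, and neither the size nor the direction of any imbalance can be derived. The figures above show only how sensitive small counts are to reporting, under assumed arm size, event rates and reporting rates.

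This is a design choice that should be improved because the contacts needed already exist. It does not undermine the other feasibility objectives.

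**What to change.** In Feasibility outcomes and in Data monitoring and interim analyses:

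1. At every assessment already planned, in both arms, have the research assistant ask the same short, accessible, non-leading question about anything that has got worse or been upsetting since the last contact.
2. Have the therapist note any distress in or at the end of a session alongside the recording of attendance.
3. Name the incident log, the MOAS self-aggression item and the symptom scales as harm data.
4. Report solicited harms by arm over the same period. Report therapist-noted in-session distress separately, since it can arise in one arm only.
5. Keep spontaneous reporting, including the research team and PALS routes, as an addition.

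The cost is slightly more data collection and a protocol amendment, which under Protocol amendments goes to the ethics committee whether substantial or not. Recorded harm counts may also look less favourable than under the passive route.
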